## Abstract

To date, no psychotropic medication has shown to effectively halt progression to psychosis among individuals at Clinical High-Risk for psychosis (CHR), fueling the search for novel therapeutic agents. Recent evidence supports Palmitoylethanolamide (PEA) signaling as a potential psychosis biomarker, also indicating a therapeutic role for its supplementation in the treatment of psychotic disorders. Nonetheless, the effect of sustained PEA intake in CHR subjects has never been explored so far. We will assess the feasibility of enrolling 20 CHR young adults presenting with attenuated psychotic symptoms (APS) in a 12-week, open-label, investigator-initiated, proof-of-concept, single-arm trial of ultramicronized-PEA (um-PEA) 600 mg/day. Once completed the 12-week phase, participants will be proposed to enter a 24-week extension phase of the study. We will examine um-PEA ability to reduce APS and psychic distress, um-PEA safety and tolerability, and the biological basis of um-PEA effect in terms of modulation of inflammatory response, endocannabinoid (eCB) signaling, and microbiome composition. Our trial aims to address an unmet clinical need in CHR subjects, providing an initial solid basis for the development of future studies evaluating the efficacy and tolerability of PEA supplementation in this group of patients.

## 1. Introduction

The Clinical High-Risk (CHR) for psychosis state has been first described over two decades ago and represents the phase preceding the potential development of full-blown psychosis [1]. Recent meta-analyses of risk of transitioning to psychosis at 2 years among CHR individuals show rates of approximately 16–19%, while risk factors accumulation (*risk enrichment*) results in increasing rates of up to 35% at 10 years [2,3]. Compared to the outdated “prodrome” concept, the CHR paradigm provides a less deterministic understanding of schizophrenia (SCZ), thus highlighting the importance of detection, assessment, and early intervention on milder symptoms preceding psychosis onset to halt disease progression [4,5,6]. However, to date, no psychotherapeutic or psychopharmacological interventions have shown to effectively prevent progression to psychosis among CHR subjects [3,7], nor to relieve them from attenuated psychotic symptoms (APS) [8], negative symptoms [9], or impaired global functioning [10]. Compelling evidence of the endocannabinoid (eCB) system early disruption in the neurophysiological pathway leading to schizophrenia onset has fostered the search for novel medications (e.g., cannabidiol, CBD) targeting the eCB system for both psychosis patients and CHR individuals [11,12,13,14,15,16].

To this extent, growing research is focusing on the role of the eCB-like compound Palmitoylethanolamide (PEA) as a potential therapeutic agent in the context of several neuropsychiatric conditions [17,18,19]. PEA is a naturally occurring N-Acylethanolamine (AE), proven to modulate the central and peripheral neuroimmune systems and to exert protective functions against glutamate neurotoxicity [20,21,22]. It directly activates the Peroxisome Proliferator Activated Receptor-α (PPAR-α) and G protein-coupled receptor 55 (GPR55), allosterically modulates the Transient Receptor Potential Vanilloid 1 (TRPV1), and indirectly interacts with type 1- (CB1) and type 2- (CB2) cannabinoid receptors [23], sharing similar pharmacodynamic properties with the phytocannabinoid CBD [24]. We recently conducted a systematic review aimed at investigating the biobehavioral role of PEA in psychotic disorders [25]. Overall, evidence from clinical studies included in our reappraisal converges on the involvement of PEA in different psychotic phenotypes. A robust strain of research indicates an endogenous attempt of PEA to restore homodynamic balance under disease conditions in CHR individuals [26], non-affective psychosis patients [27,28,29,30], and affective psychosis patients [28,31] at different stages of illness. Specifically, PEA blood tone would increase in the initial phases of a psychotic disorder, while subsiding concomitantly to disease progression. Consistently, PEA levels in the central nervous system (CNS) were found to be elevated in the early stages of SCZ [32], before declining as the disease progresses [33]. Limited but promising evidence was also obtained from interventional studies assessing the potential of PEA therapeutic supplementation in SCZ patients [34], bipolar disorder patients with manic symptoms [35], and Parkinson’s disease patients with psychotic symptoms [36]. PEA showed a selective efficacy on negative psychotic (e.g., alogia) [34] and acute manic [35] symptoms, while not significantly ameliorating positive psychotic symptoms (e.g., delusions) [34,35,36]. To the best of our knowledge, to date there is no evidence of the effect of PEA treatment in the clinical stages preceding the onset of psychosis as well as to prevent the risk of disease progression.

We propose a feasibility study of sustained ultramicronized-PEA (um-PEA) supplementation in CHR individuals to address the lack of a first-line treatment for this group of subjects, focusing on study recruitment and patient acceptability.

## 2. Materials and Methods

### 2.1. Trial Design

This is a 12-week, open-label, investigator-initiated, proof-of-concept, single-arm study (Phase-2 Pilot Study) assessing the effect of um-PEA 600 mg/day in CHR individuals presenting with APS [1]. Within the first 12 months from the first participant recruitment, we will assess the feasibility of enrolling a minimum of 20 CHR participants and whether at least 80% of participants have completed the 12-week follow-up. After completing the initial 12-week phase, participants will be proposed to enter a 24-week extension phase of the study to evaluate the clinical stability of the treatment. Based on clinical judgement of the improvement obtained at that point, um-PEA might be titrated to 1200 mg/day. Each participant will undergo um-PEA treatment for a maximum of 36 weeks (Table 1). Our purpose is to examine: (i) um-PEA ability to alleviate APS and anxiety symptoms in CHR patients; (ii) um-PEA safety and tolerability; (iii) the biological basis of um-PEA effect. The study was approved by the Department of Medicine (DMED) at University of Udine (Institutional Review Board: 93/2023) in June 2023 (https://osf.io/wn2kf, accessed on 5 December 2024).

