### 2.2. Sample Size Calculation

The primary analysis (see below) will focus on total severity of APS as evaluated using the Comprehensive Assessment of At-Risk Mental State (CAARMS) [1], measured in three longitudinal assessments (i.e., Feasibility phase: Baseline, T1, and T2). Accepting a type-I error (α) of 5% and a type-II error (β) of 20%, we would need a sample of 8–12 participants to detect an effect of large size (partial-η2 ≥ 0.140). This value was obtained considering a moderate-to-large test-retest reliability of measurements over time (+0.500 < r ≤ +0.700) and the absence of correction for sphericity. With an intermediate sphericity correction (ε = 0.750), the required sample size would be 10–14; in the worst case (ε = 0.500), instead, 12–19 participants would be needed. We therefore propose the recruitment of 20 participants, considered coherent with a pilot study and sufficient to evaluate feasibility outcomes of clinically significant size, also considering a low drop-out rate (i.e., ≤ 20%). When large statistically significant results are obtained on total severity of APS, specific APS severities will be further investigated (i.e., considering four P1 scales). For this secondary endpoint, on average, a sample-size of 17 participants would be sufficient to detect large effects, also considering Bonferroni’s correction for multiple independent comparisons (i.e., α = 0.012). Power analyses were carried out with G*Power-3.1.9.7 [45].

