#### 2.3.2. Research Endpoints

We will primarily address whether um-PEA added to treatment as usual (TAU) in CHR patients improves APS. Our secondary research questions are whether um-PEA added to TAU in CHR patients improves APS to the extent that patients no longer satisfy the diagnostic criteria for the CHR state, relieves APS-associated distress, improves CHR-related anxiety symptoms, and ameliorates social and role functioning, as well as general psychopathology and wellbeing measures. Therefore, our primary endpoint will be the assessment of APS severity as measured using the CAARMS [1]. As per the secondary endpoints: (i) APS-associated distress will be measured using the CAARMS [1]; (ii) severity of CHR-related anxiety symptoms will be measured using the Hospital Anxiety and Depression Scale (HADS) [43]; (iii) the level of impaired global functioning will be measured using the Social and Role functioning Scale [44]; (iv) clinical remission, defined as no longer meeting the APS criteria [1] will be measured using the CAARMS [1]; (v) general psychopathology and wellbeing changes will be measured using the CAARMS [1].

All the study endpoints for the 12-week clinical trial will be assessed by comparing follow-up (FUP) visits and baseline. For those participants continuing in the 24-week extension phase, change (FUP visit minus baseline) in the severity of psychotic symptoms as measured using the CAARMS will be compared with the group of those willing to discontinue um-PEA and continue with TAU. Should the psychopathological condition require TAU adjustments based on clinical judgement, this will be mentioned in a specific section of the trial case report form (CRF; https://osf.io/2vayh, accessed on 5 December 2024).

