### 2.8. Statistical Methods

#### 2.8.1. Data Verification, Statistical Monitoring, and Analysis

At the study start, a structured data verification plan will be agreed and developed by the Head Statistician ([name]) of the research team. Quality of data will be routinely checked in terms of consistency across paper- and electronic-based entry systems. Statistical monitoring will include patient severity level, eventual withdrawals, baseline data, FUP visits data, and adverse effects. The research team will approve a Statistical Analysis Plan within the early stages of the study, and before the Head Statistician summarizes any data (i.e., with univariate and repeated measures analysis, including preliminary assessment and management of any outliers and assessment of the metric qualities of measurements, such as normality and sphericity, where necessary). Proportions will be presented for each feasibility outcome. Interim analyses are not planned. The Head Statistician will both carry out and interpret statistical analysis. Our primary analysis will involve a generalized linear model with CAARMS psychotic symptom severity as the dependent measure and time as a repeated measure (possibly supplemented with analyses at the participant level, as random effects in mixed models). We are interested in whether there is a significant benefit over time with um-PEA treatment: therefore, particular interest will be placed on time as a fixed factor on the severity of outcomes. CAARMS distress and total score as well as HADS and GF ratings will be analysed in a similar manner. We will also conduct paired tests (both parametric and non-parametric) based on baseline and endpoint assessments to examine measures of CAARMS severity, CAARMS frequency/duration, and secondary outcomes. Trend and rates of adverse effects will be reported, as well as reasons for dropouts from the trial.

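### The extension is meant to evaluate clinical stability, but the one comparison written for it does not by itself show whether continuers kept their week-12 improvement

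*Protocol article*

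**What the plan says.** - **Aim.** Section 2.1 (Trial Design) says that after the first 12 weeks participants will be invited to "enter a 24-week extension phase of the study to evaluate the clinical stability of the treatment". It attaches no definition of stability and no tolerated loss.
- **Extension analysis.** Section 2.3.2 (Research Endpoints) names the outcome, "change (FUP visit minus baseline) in the severity of psychotic symptoms as measured using the CAARMS", and says that this "will be compared with the group of those willing to discontinue um-PEA and continue with TAU". Table 1 labels Day 0 as Baseline, so the anchor is the start of treatment and not week 12.
- **Within-person comparison.** The same section confines the general rule to the first phase: "All the study endpoints for the 12-week clinical trial will be assessed by comparing follow-up (FUP) visits and baseline".
- **Primary analysis.** Section 2.2 describes total APS severity as "measured in three longitudinal assessments (i.e., Feasibility phase: Baseline, T1, and T2". Section 2.8.1 gives a "generalized linear model with CAARMS psychotic symptom severity as the dependent measure and time as a repeated measure" and does not say whether it also covers T3 and T4.
- **Supplementary tests.** Section 2.8.1 adds: "We will also conduct paired tests (both parametric and non-parametric) based on baseline and endpoint assessments". It names no contrast that starts at T2.
- **Data.** Table 1 schedules CAARMS at Baseline, T1, T2, T3 and T4.

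**The concern.** On its natural reading, stability asks whether people who stay on um-PEA still have at weeks 24 and 36 what they had at week 12. That is a question about change after T2 within continuers. The written contrast answers a different one: how far continuers and stoppers differ in total change since Day 0. It mixes the change before T2 with the change after it, and it subtracts whatever the stoppers do.

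The risk lies in interpretation. A difference in favour of continuing could be reported as stability although continuers had lost ground and stoppers had lost more. A null difference could be reported as stability although both groups had relapsed alike. Random allocation between continuing and stopping, or a week-12 reference, would still leave the between-group difference dependent on the stoppers. The point is therefore separate from self-selection and from the choice of reference visit.

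**Working it through.** **1. The plan's own figures.** The extension has no stated sample size. The 12-week sample sizes in section 2.2 were checked first, using noncentral F for one group with m = 3 visits:

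- f² = 0.14 / (1 − 0.14) = 0.163, so f = 0.403
- λ = f² · n · m · ε / (1 − r), df1 = (m − 1)ε, df2 = (n − 1)(m − 1)ε, α = 0.05, power 0.80

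With r = 0.7 and 0.5 this gives 8 and 12 (ε = 1), 10 and 14 (ε = 0.75), and 12 and 19 (ε = 0.5). All six match. They concern Baseline, T1 and T2 only.

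**2. The written extension contrast.** Let C and S be mean CAARMS severity in continuers and stoppers, with the subscript giving the visit (0 = Day 0, 4 = T4):

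D = (C4 − C0) − (S4 − S0)

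Let g be the week-12 improvement, taken as equal in both groups. A negative change is an improvement.

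| Course after week 12 | C4 − C0 | S4 − S0 | D |
|---|---|---|---|
| Both keep the gain | −g | −g | 0 |
| Both lose all of it | 0 | 0 | 0 |
| Continuers keep, stoppers lose all | −g | 0 | −g |
| Continuers lose all, stoppers end g worse than Day 0 | 0 | +g | −g |
| Continuers lose all, stoppers keep | 0 | −g | +g |

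Rows 1 and 2 share a value of D, and so do rows 3 and 4, yet within each pair the continuers did opposite things. Comparing row 3 with row 2 (stoppers lose all in both), or row 1 with row 5 (stoppers keep in both), D moves by the full g. With the stoppers held fixed, the contrast does respond to the continuers.

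**3. Size under assumed values.** The document gives no continuer/stopper split, SD or expected gain. Assumed here: g = 1 SD of the change score, equal SDs, and a two-sided two-sample t test at 5%. There were 20,000 simulated trials per scenario. Twenty recruits with up to 20% dropout leave 16 to 20 people, so a 10:10 and a 12:4 split are shown.

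| Scenario | Rejection, 10:10 | Rejection, 12:4 |
|---|---|---|
| Both keep | 4.7% | 5.0% |
| Both lose all | 5.2% | 4.9% |
| Continuers keep, stoppers lose all | 55.9%, favours continuing | 36.8%, favours continuing |
| Continuers lose all, stoppers 1 SD worse than Day 0 | 57.3%, favours continuing | 36.4%, favours continuing |
| Continuers lose all, stoppers keep | 55.8%, against continuing | 36.2%, against continuing |

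The first two rows equal the significance level by construction. They illustrate the algebra and are not separate evidence.

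**4. The direct contrast.** The 95% interval for mean T4 − T2 in n continuers has half-width t(0.975, n − 1) / √n, in SDs of that change. For n = 10 this is 2.262 / 3.162 = 0.72. For n = 20, 16, 12 and 8 it is 0.47, 0.53, 0.64 and 0.84. In SDs of the score itself, multiply by √(2(1 − r)). At n = 10 this gives 0.72 × 1.00 = 0.72 (r = 0.5) and 0.715 × 0.775 = 0.55 (r = 0.7).

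**The case against.** **The contrast is not blind to the continuers.** A reader might infer that the written comparison gives the same answer whether continuers keep or lose their gain. It does so only if stoppers shift by the same amount. With the stoppers' course fixed, it moves by the full gain and can change sign. That stronger claim does not hold. For the same reason, a null result is not equally likely under stability and complete loss in general.

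**The article names no test and no decision rule.** It says only that changes will be compared, and no-worsening is an interpretation of stability. Both are fair points. The t test above is an assumption, and the article does not commit itself to reading a significant difference as stability.

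**The information is not lost.** For the same participants, T4 minus baseline less T2 minus baseline is T4 minus T2, and CAARMS is scheduled at all three visits. It would therefore be wrong to infer that the extension cannot answer its question. The data allow it; the written comparison does not do it.

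**A later analysis plan may supply the contrast.** Section 2.8.1 promises one, and it is not shown. The repeated-measures model might also be extended to T3 and T4. A missing margin or contrast is therefore not held against the article. What remains is that section 2.3.2 does not leave the extension analysis open. It fixes outcome, anchor and comparator, and these do not match the aim in section 2.1.

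**A formal stability rule is ambitious for about 10 people.** This stands. With a tolerated loss of half of an assumed 1 SD gain (here 1 SD of the score), 10 continuers would demonstrate true stability in only about 29% (r = 0.5) to 45% (r = 0.7) of trials.

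**Conclusion.** The point holds in a limited form. Stability is the stated aim of the extension, and the only comparison written for it does not isolate what continuers do after week 12, because it also depends on the stoppers. Opposite courses in continuers can give the same expected difference: zero in one pair, and the full gain in favour of continuing in the other. The algebra needs no assumption beyond an equal week-12 gain in both groups. The rejection rates rest on the assumed split, SD and 1 SD gain, and on reading the comparison as a t test. The scenario in which stoppers end below their starting level illustrates what is possible and is not a forecast.

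This concerns a secondary phase of a pilot and does not touch the 12-week primary analysis. It is worth correcting because the remedy costs almost nothing and prevents a misleading stability statement. Section 2.1 also allows the dose to change during the extension, so any stability estimate describes continued treatment as given and not one fixed regimen.

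**What to change.** In section 2.3.2, and in the analysis plan:

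- For the stability aim, report the change in CAARMS severity from T2 to T3 and from T2 to T4 within participants who continue um-PEA, each with a 95% confidence interval.
- Keep the comparison with those who stop, but label it descriptive and state that it is not evidence of stability.
- If the report is to claim that stability was shown, fix a tolerated loss in CAARMS points before any data are seen, and make the claim only if the worsening end of the interval lies below it. Otherwise give the estimate and interval without that claim.

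The cost is a few lines of text and no new visits or measurements. The downside is precision. With about 10 continuers the half-width is about 0.72 SD of the T2-to-T4 change, or 0.55 to 0.72 SD of the score for r from 0.7 to 0.5. Stability will therefore often remain unproven even when it is real.

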### 2.2. Sample Size Calculation

The primary analysis (see below) will focus on total severity of APS as evaluated using the Comprehensive Assessment of At-Risk Mental State (CAARMS) [1], measured in three longitudinal assessments (i.e., Feasibility phase: Baseline, T1, and T2). Accepting a type-I error (α) of 5% and a type-II error (β) of 20%, we would need a sample of 8–12 participants to detect an effect of large size (partial-η2 ≥ 0.140). This value was obtained considering a moderate-to-large test-retest reliability of measurements over time (+0.500 < r ≤ +0.700) and the absence of correction for sphericity. With an intermediate sphericity correction (ε = 0.750), the required sample size would be 10–14; in the worst case (ε = 0.500), instead, 12–19 participants would be needed. We therefore propose the recruitment of 20 participants, considered coherent with a pilot study and sufficient to evaluate feasibility outcomes of clinically significant size, also considering a low drop-out rate (i.e., ≤ 20%). When large statistically significant results are obtained on total severity of APS, specific APS severities will be further investigated (i.e., considering four P1 scales). For this secondary endpoint, on average, a sample-size of 17 participants would be sufficient to detect large effects, also considering Bonferroni’s correction for multiple independent comparisons (i.e., α = 0.012). Power analyses were carried out with G*Power-3.1.9.7 [45].

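### Section 2.2 attaches the label partial-η² 0.14 to sample sizes that fit a much larger time effect; the effect size or the stated power needs restating, with N = 20 kept

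*Protocol article*

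**What the plan says.** Section 2.2 (Sample Size Calculation) sizes the trial on total APS severity by CAARMS, taken at Baseline, T1 and T2, with α 5% and β 20%. It states that "we would need a sample of 8–12 participants to detect an effect of large size (partial-η2 ≥ 0.140"). It adds that the figure was reached "considering a moderate-to-large test-retest reliability of measurements over time (+0.500 < r ≤ +0.700) and the absence of correction for sphericity". Two further ranges follow: "With an intermediate sphericity correction (ε = 0.750), the required sample size would be 10–14", and "in the worst case (ε = 0.500), instead, 12–19 participants would be needed". From these it proposes 20 participants, also citing coherence with a pilot study and a drop-out of at most 20%. For the four separate P1 scales it gives 17 participants on average at a Bonferroni level of 0.012. The software is G*Power 3.1.9.7; the effect-size option is not named.

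Section 2.3.2 names APS severity as the primary endpoint, and section 2.8.1 makes time, as a repeated measure in a single group, the effect of main interest.

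**The concern.** The partial-η² of a repeated-measures time effect is SS_time / (SS_time + SS_error), where SS_error is the subject-by-time residual. Correlation between visits shrinks that residual. Once partial-η² is fixed, the correlation has done its work, and power depends only on N, the number of visits and ε. A required N that moves from 12 to 8 as r goes from 0.5 to 0.7, at the same partial-η², therefore shows that the correlation has been used a second time.

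At stake is the meaning of the only formal power statement for the primary efficacy endpoint. A reader who takes 0.14 at face value will believe that 20 participants comfortably exceed what is needed for an effect of that size. The same method carried into the larger study foreseen in the Discussion would undersize it.

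**Working it through.** **Inputs (all from section 2.2).** α = 0.05; power 0.80; partial-η² = 0.14, so f² = 0.14/0.86 = 0.1628 and f = 0.4035; m = 3 visits, one group; r = 0.5 to 0.7; ε = 1, 0.75, 0.50; N = 20, or 16 after 20% drop-out.

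**Test.** Noncentral F with df1 = 2ε and df2 = 2(N−1)ε.

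**Step 1: reproduce the plan.** Take λ = f²·3N·ε/(1−r), with r entered separately. The smallest N reaching 80% power is:

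| ε | r = 0.5 | r = 0.7 | Plan |
|---|---|---|---|
| 1 | 12 | 8 | 8–12 |
| 0.75 | 14 | 10 | 10–14 |
| 0.50 | 19 | 12 | 12–19 |

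All six limits match. Using the rounded value f = 0.40 gives 15 instead of 14 at ε = 0.75 and r = 0.5, so the match points to 0.14 itself having been converted to f.

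**Step 2: the effect this formula powers.** Here f² is the variance of the visit means divided by the raw-score variance. The residual variance is the raw-score variance times (1−r). The ratio SS_time/SS_error is then about q = 3f²/[2(1−r)], and partial-η² = q/(1+q).

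- r = 0.5: q = 0.1628 × 1.5/0.5 = 0.488, giving 0.33.
- r = 0.7: q = 0.1628 × 1.5/0.3 = 0.814, giving 0.45.

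With equal steps across the three visits, f = 0.4035 is a total fall of 2 × 0.4035 × √1.5 = 0.99 raw-score SD.

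**Step 3: take 0.14 as the within-subject partial-η².** Now λ = f²·2(N−1)·ε, without r.

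| ε | N for 80% | Power, N = 20 | Power, N = 16 |
|---|---|---|---|
| 1 | 33 | 56% | 45% |
| 0.75 | 39 | 48% | 39% |
| 0.50 | 52 | 39% | 31% |

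At the plan's own numbers, power is 33% for 12 and 21% for 8 (ε = 1), and 37% for 19 (ε = 0.50).

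Using N instead of N−1 in λ gives 32, 38 and 51 for 80% power, and 59%, 50% and 40% with 20. A simulation under compound symmetry (20,000 runs, ε = 1, N = 20), scaled by that second convention, gave 58% power at r = 0.5 and 59% at r = 0.7. Power does not depend on r once partial-η² is fixed.

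**Step 4: partial-η² detectable with 80% power** (Step 3 formula, solved for the effect; ε = 1, 0.75, 0.50).

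- N = 20: 0.216, 0.253, 0.315.
- N = 16: 0.262, 0.306, 0.375.

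**Step 5: the secondary figure of 17.** At α = 0.012, the Step 1 formula gives 16, 20, 27 (r = 0.5), 14, 17, 22 (r = 0.6) and 11, 13, 18 (r = 0.7) for the three ε values. The mean is 158/9 = 17.6, close to the stated 17. The averaging grid is my assumption, since the plan does not give one. The figure appears to rest on the same conversion.

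**The case against.** The strongest reply is that this is a label, not a miscalculation. The arithmetic is exact for the formula used, and r is stated openly as an input, which fits an effect of f ≈ 0.40 on the raw-score SD scale. On that reading 20 participants have 84–97% power at ε = 0.50 and more at higher ε. This stands, and it makes the finding conditional. A reader might infer that the trial simply has 39–56% power; the document does not support that without the condition that 0.14 is the within-subject partial-η². It does call it partial-η², however, so the text needs changing on either reading.

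The trial is also a feasibility study, with recruitment and completion criteria in section 2.1, and 20 is defended partly on pilot grounds. That limits the consequence but does not excuse a wrong power statement for a named primary endpoint. Nothing in the article says that a null result would be read as excluding a large effect.

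Two stronger inferences are tempting and fail:

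- With 20 participants and ε = 1, significance needs an observed partial-η² of 0.146, so a reader might conclude that 80% power at 0.14 is impossible. That confuses the observed with the true value. The observed one tends to run high (simulated median 0.167), and power at a true 0.14 is 56% although the threshold lies above it. The conclusion rests on the noncentral F calculation alone.
- The article says "When large statistically significant results are obtained on total severity of APS, specific APS severities will be further investigated". A reader might infer that the condition of largeness filters nothing and should go. The sentence does not restate 0.14 as its threshold. Section 2.1 plans at least 20, and with 21 analysed the critical value is already 0.139. Dropping the trigger does not follow from the power error.

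Finally, the figures for 16 assume complete cases. Section 2.8.2 keeps everyone with one post-baseline measure and section 2.8.1 allows mixed models, so some drop-outs would still contribute data.

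**Conclusion.** The statement is wrong as written: the sample sizes and the effect-size label in section 2.2 do not belong together. Read literally, the requirement is understated by a factor of roughly 2.7 to 4 (33 against 8–12, 39 against 10–14, 52 against 12–19), and 20 participants fall short of 80% power at every ε. Read as f ≈ 0.40, the numbers are right and the effect is understated: the partial-η² powered for is more than twice to three times the one printed.

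The G*Power option is inferred from the exact match on all six limits. The choice between N and N−1 in λ shifts power by about 2–3 points and does not alter the conclusion. The finding does not call for a larger trial and does not touch the feasibility criteria.

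**What to change.** Keep N = 20 and reword section 2.2 in one of two ways:

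1. Keep partial-η² as the scale, and replace the three ranges with the effect detectable at 80% power: about 0.22–0.32 with 20 participants and 0.26–0.38 with 16 complete cases, across ε from 1 to 0.50.
2. Keep the ranges, state that the assumed effect is f ≈ 0.40 on the raw-score SD scale, and give its implied within-subject partial-η² of about 0.33 (r = 0.5) to 0.45 (r = 0.7).

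In both cases name the G*Power effect-size option, and restate the secondary figure of 17 on the same scale, with the r and ε values over which it was averaged.

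The cost is wording in the protocol, and in the analysis plan if it repeats the figures. No participants, visits or tests change; the stated sensitivity becomes less favourable.

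### Twenty recruits with the allowed 20% drop-out leave 16 complete cases, below the plan's own 19 (top of the primary worst case) and below the 17 given for the four scales, which is only an average over scenarios

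*Protocol article*

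**What the plan says.** Section 2.2 of the protocol article sizes a repeated-measures analysis of total APS severity. Its terms are "Accepting a type-I error (α) of 5% and a type-II error (β) of 20" per cent, "to detect an effect of large size (partial-η2 ≥ 0.140"), and an outcome "measured in three longitudinal assessments (i.e., Feasibility phase: Baseline, T1, and T2"). The correlation is described as "moderate-to-large test-retest reliability of measurements over time (+0.500 < r ≤ +0.700"). The printed requirements are 8–12 without a sphericity correction, 10–14 at ε = 0.75, and "in the worst case (ε = 0.500), instead, 12–19 participants would be needed".

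From these the section concludes that 20 should be recruited, "also considering a low drop-out rate (i.e., ≤ 20" per cent. For the four P1 scales, tested at a Bonferroni level printed as 0.012, it adds that "on average, a sample-size of 17 participants would be sufficient to detect large effects". It prints no range by ε or correlation for the scales, and shows no inflation for drop-out anywhere.

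Section 2.1 sets completion of the 12-week follow-up by at least 80% of participants as a feasibility criterion, which is 16 of 20. Section 2.8.2 keeps in each analysis everyone with at least one post-baseline measure.

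**The concern.** The recruitment figure exceeds the largest primary requirement by one participant, yet the same sentence allows for losing up to four. The trial could meet its own completion criterion and still have fewer complete cases than two of the sample sizes it prints.

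The figure for the scales has a second weakness. The primary requirement is shown as a range for each ε, whereas the scale requirement is collapsed to one average. An average of requirements leaves every scenario above it short of 80% power. A reader who takes 17 as sufficient could treat a non-significant scale result as coming from an adequately powered test when it did not.

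**Working it through.** **Drop-out arithmetic, from printed figures only.** 20 × (1 − 0.20) = 16, and 16 < 17 < 19. With 20 recruits, keeping 19 tolerates 1 − 19/20 = 5% drop-out, and keeping 17 tolerates 1 − 17/20 = 15%. Inflating for 20% would give 19/0.8 = 23.75, so 24 recruits, and 17/0.8 = 21.25, so 22.

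**Formula.** G*Power's default for repeated-measures ANOVA (within factors, one group, m = 3) uses a noncentral F with
- f² = 0.14/0.86 = 0.1628
- λ = f² · N · m · ε/(1 − r)
- df1 = (m − 1)ε and df2 = (N − 1)(m − 1)ε.

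The required N is the smallest with power of at least 0.80.

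**Reproducing the plan (α = 0.05).**

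| ε | r = 0.5 | r = 0.6 | r = 0.7 | Printed |
|---|---|---|---|---|
| 1 | 12 | 10 | 8 | 8–12 |
| 0.75 | 14 | 12 | 10 | 10–14 |
| 0.5 | 19 | 15 | 12 | 12–19 |

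All six printed end points are matched. The options without the correlation term give 32–52 and do not match, so this is the calculation the plan used.

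**Primary power with 16 complete cases (α = 0.05).**

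| ε | r = 0.5 | r = 0.6 | r = 0.7 |
|---|---|---|---|
| 1 | 0.930 | 0.972 | 0.994 |
| 0.75 | 0.864 | 0.929 | 0.978 |
| 0.5 | 0.743 | 0.832 | 0.921 |

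For the lowest cell, λ = 0.1628 × 16 × 3 × 0.5/0.5 = 7.81 with 1 and 15 degrees of freedom, giving 0.743. With 19 it is 0.821 and with 20 it is 0.842. At ε = 0.5, power at 16 reaches 0.80 at r of about 0.57.

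**Requirement for the four scales, same formula.** The plan prints α = 0.012; 0.05/4 = 0.0125.

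| ε | r = 0.5 | r = 0.6 | r = 0.7 |
|---|---|---|---|
| 1 | 16 | 14 | 11 |
| 0.75 | 20 | 17 | 13 |
| 0.5 | 27 | 22 | 17 (18 at α = 0.012) |

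At 0.0125 the mean is 157/9 = 17.4 over the nine cells and 104/6 = 17.3 over the six end points. At 0.012 it is 17.6 and 17.5. The range is 11–27 at either level.

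**Per-scale power (α = 0.0125), 16 complete cases / all 20.**

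| ε | r = 0.5 | r = 0.6 | r = 0.7 |
|---|---|---|---|
| 1 | 0.805 / 0.911 | 0.900 / 0.966 | 0.971 / 0.994 |
| 0.75 | 0.681 / 0.816 | 0.798 / 0.906 | 0.914 / 0.973 |
| 0.5 | 0.503 / 0.644 | 0.618 / 0.760 | 0.767 / 0.885 |

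With 16, four of the nine cells reach 0.80: all three at ε = 1, and ε = 0.75 with r = 0.7. The cell at ε = 0.75, r = 0.6 misses by a hair. With exactly 17, power at ε = 0.5, r = 0.5 is 0.541 (0.534 at α = 0.012).

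**The case against.** The drop-out clause can be read as qualifying the feasibility outcomes and not the power calculation, and nowhere does the article promise 80% power in every scenario after maximum drop-out. That ambiguity is real. Still, the sentence presents 20 as following from the power ranges, and the 17 is separately described as enough to detect large effects.

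Sixteen is a floor, because 20% is an upper bound. Section 2.8.2 retains anyone with one post-baseline measure, section 2.8.1 allows mixed models, and section 2.9 continues follow-up for those who stop treatment. The information lost may therefore be less than four whole participants. This stands and softens the primary shortfall. It does not close the gap, because the calculation assumes all three visits, and section 2.2 claims no credit for partial data.

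The correlation is stated as strictly above 0.5, so 19 is a boundary value. At r = 0.51 the worst case needs 18 and at r = 0.55 it needs 17, both still above 16.

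The article does say that 17 is an average, and at α = 0.0125 that number reaches 80% in six of the nine cells. Calling it insufficient everywhere would be wrong.

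A reader might infer that the primary analysis is underpowered in general, or that the scales cannot support testing whenever sphericity fails. Neither follows. Sixteen covers every primary scenario at ε = 1 and 0.75, and it gives 91% per-scale power at ε = 0.75, r = 0.7.

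**Conclusion.** Wrong as written, of moderate to minor severity. On the plan's own figures, the allowed drop-out leaves 16 complete cases against stated needs of up to 19 and of 17.

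For the primary endpoint the effect is confined to ε = 0.5 with r below about 0.57, where power is 74–80%. For the four scales it is larger: power at 16 spans 50% to 97%, and at ε = 0.5 no correlation in the stated range reaches 80%. In the least favourable cell even all 20 completing gives only 64%.

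The severity is limited because this is a feasibility pilot and the scales are examined only after a large significant primary result. The conclusion assumes the G*Power default calculation, which the exact match supports, and treats drop-outs as contributing nothing, which is conservative. The 11–27 range is reconstructed from the plan's inputs. Whether that effect-size convention suits this design is a separate matter and is not judged here.

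**What to change.** Keep 20 recruits and restate section 2.2:
- Say that at the maximum allowed drop-out at least 16 complete cases remain, and that participants with partial data also enter the analysis.
- Tabulate primary and per-scale power at 16 and at 20 by ε and r.
- Replace the average of 17 by the range of requirements: 11–16 at ε = 1, 13–20 at ε = 0.75, and 17–27 at ε = 0.5 (18–27 if α = 0.012 is kept).
- Describe the scale tests as exploratory for those combinations of ε and r in which 16 gives less than 80% power, not for every ε below 1.

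The change is to wording only. It needs no extra participants, and its one cost is that the stated power becomes less favourable.
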